### Allocation concealment

The allocation sequence is concealed using SurveyMonkey® software based on a commercial, but unknown algorithm without a pre-identified sequence.

### Blinding

Participants will know that the trials are testing different formats to present health recommendations but will be blinded with respect to what formats are being compared and to the group to which they are allocated. Participants will not be aware of their random allocation to the PLR or SLV format until disclosure. Thus, participants will be blinded for all outcomes except the secondary outcome of preference. We will blind data analysts involved in data interpretation and manuscript writing to reduce bias in data analysis and interpretation [25, 26]. To reduce bias, we will draft each population’s manuscript with general group labels (i.e., group A vs B) and agree on the final interpretation before the group allocation (optimized PLR or SLV) is revealed.

### Sample size calculation

The sample size was calculated using the primary outcome of understanding. For this two-sided (*α* = 0.05) superiority analysis, these computations were made based on a *t*-test with the null hypothesis that there is no difference between the PLR version and the SLV in understanding of information.*H*_*0*_*:* PLR version = SLV*H*_*1*_*:* PLR version ≠ SLV

We will determine whether we can reject the null hypothesis of no difference in understanding between the formats of presenting recommendations. We assume a correct response rate (regarding the understanding of information) of 75% in the PLR arm and 60% in the control arm [relative risk =1.25] based on a recent RCT and prior trials on plain language summaries (PLS) of summary of findings table [19, 23]. With typical alpha (0.05) and beta (0.8) parameters and an allocation ratio of 1:1, 240 participants (120 in each arm) would be required (Stata/SE 16.0) [27]. Assuming 15% non-completion, we will recruit 282 participants from each population and adjust this number if non-completion is higher.

Since we are using two different recommendation topics with each population, we might observe an interaction between the recommendation topic and our outcome of understanding. Thus, when we reach half of our intended sample size, we will conduct an interim analysis for a possible interaction effect. If the data suggests that there might be an interaction, we will consider modifying our initial sample size. This new sample size cannot be determined in advance since we cannot anticipate the magnitude of the potential interaction effect, but it will be determined based on published guidance on power calculations for credible subgroup effects [28]. If needed, we will submit an amendment that explains the new sample size and need for additional recruitment based on the magnitude of the interaction effect identified. In summary, an enhanced sample size, if indicated and feasible, will allow us to conduct a more meaningful analysis by exploring the results by topic of recommendation.

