## Methods

We will follow a multi-methods approach: randomized controlled trials (RCTs) with qualitative interviews among a subset of participants. The trials are pragmatic allocation-concealed, blinded superiority RCTs with at least 240 participants in each population (parents, adult, and youth). The trials were preceded by preparatory engagement work with Canadian youth advisors, a Canadian parent advisory group, and an international adult Cochrane Consumer group, herein referred to as stakeholder groups. The youth site’s preparatory engagement work was co-developed and implemented by two youth partners ([name]) in collaboration with LS, to ensure meaningful engagement efforts were embedded into the research process. We gathered input from stakeholders on COVID-19 priority topics and PLR content and format. Input from stakeholders helped us refine the PLR format to be evaluated with each population in the trial.

We will conduct qualitative interviews with a subset of the participants who completed the trials to help contextualize the digital user experience and understand the results of the trial.

Any amendments to this protocol will be made available via medRxiv.

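### The 240 participants (120 per arm) fit a one-sided 5% test; for the stated two-sided 5% test of 75% vs 60% they give about 70% power, not 80%

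*Protocol article*

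**What the plan says.** All the inputs stand in the protocol article under Sample size calculation.

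- **Test:** "For this two-sided (*α* = 0.05) superiority analysis", with a "null hypothesis that there is no difference between the PLR version and the SLV in understanding of information" and a not-equal alternative.
- **Assumed effect:** "We assume a correct response rate (regarding the understanding of information) of 75% in the PLR arm and 60% in the control arm".
- **Result:** "With typical alpha (0.05) and beta (0.8) parameters and an allocation ratio of 1:1, 240 participants (120 in each arm) would be required". The 0.8 labelled beta can only be meant as power.
- **Recruitment:** 240 is raised to 282 to allow for 15% non-completion.

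The same section says the computation rested on a t-test but gives no standard deviation. The Methods section repeats the target, describing "pragmatic allocation-concealed, blinded superiority RCTs with at least 240 participants in each population". Under Inferential analysis, understanding is compared between arms by chi-square tests and risk differences with 95% confidence intervals, with significance at p < 0.05. Under Statistical analysis, each population is analysed separately.

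**The concern.** The section prints a complete set of inputs and a result that they do not produce. The printed result is what the same rates give when the whole 5% is placed in one tail. If the test is two-sided, as the protocol says throughout, the 80% power claim for the primary outcome is not a property of the design.

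This matters in three places:

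- Each population is its own trial, so the claim is made three times. A reader who meets a null result in one population will read it against a type II error of 20%.
- The recruitment target of 282 is derived from 240.
- The section plans to reconsider the sample size after an interim look at half the intended sample. Any re-sizing would start from a wrong baseline.

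**Working it through.** **Inputs** (all from Sample size calculation): p1 = 0.75, p2 = 0.60, difference 0.15, 1:1 allocation, alpha 0.05 two-sided, power 0.80.

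**Formula** (two proportions, pooled variance under the null):

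n per arm = [z_a × √(2·p̄·(1−p̄)) + z_b × √(p1(1−p1) + p2(1−p2))]² / (p1 − p2)²

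The components are:

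- p̄ = 0.675, so √(2 × 0.675 × 0.325) = √0.43875 = 0.6624
- √(0.1875 + 0.2400) = √0.4275 = 0.6538
- z_b = 0.8416 and 0.15² = 0.0225

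**Step 1: reproduce the plan's figure.** With z_a = 1.645 (one-sided 5%):

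(1.645 × 0.6624 + 0.8416 × 0.6538)² / 0.0225 = (1.0895 + 0.5503)² / 0.0225 = **119.5**, so 120 per arm and 240 in total.

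**Step 2: use the stated two-sided test.** With z_a = 1.960:

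(1.2982 + 0.5503)² / 0.0225 = **151.9**, so 152 per arm and 304 in total.

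**Step 3: try other methods.** Totals for 80% power:

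| Method | Two-sided 5% | One-sided 5% |
|---|---|---|
| Pooled variance | 304 | 240 |
| Unpooled variance | 300 | 236 |
| Arcsine | 304 | 240 |
| Log relative risk | 316 | 250 |
| Continuity-corrected | 330 | 266 |
| t-test on a 0/1 response | 300 | 236 |

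No two-sided method comes near 240.

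**Step 4: power at 120 per arm.**

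- Two-sided: (0.15 × √120 − 1.2982) / 0.6538 = (1.6432 − 1.2982) / 0.6538 = 0.528, and Φ(0.528) = **70.1%**.
- One-sided: (1.6432 − 1.0895) / 0.6538 = 0.847, and Φ(0.847) = **80.1%**.
- Exact enumeration of the Pearson chi-square test also gives 70.1% two-sided. The unpooled formula, or a t-test on a 0/1 response, gives 71.0%.

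**Step 5: recruitment.** 240 / 0.85 = 282.4, so the step from 240 to 282 is sound apart from rounding down. The two-sided counterpart is 304 / 0.85 = 357.6, or 358. The stated 240 falls short of 304 by 64, and 64/304 = 21%. Even if all 282 were analysed (141 per arm), two-sided power would be 77.0%.

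**Step 6: does the t-test wording explain 240?** A difference of 15 points on seven items is 0.15 × 7 = 1.05 items. For 120 per arm to be the size that gives 80% two-sided power, the standard deviation of the proportion correct would have to be 0.15 × √60 / (1.960 + 0.8416) = 0.415, which is 0.415 × 7 = 2.9 items on the 0-7 score. The document states no such value.

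**The case against.** The strongest objection concerns the consequence, not the arithmetic. The Outcomes section defines understanding as seven items scored 0 to 7, and the sample size section names a t-test. If the mean score is compared, a participant supplies more information than one yes/no response, and real power may be well above 70%. For 1.05 items at 120 per arm, it would be about 98% with an assumed standard deviation of 2.0 items, and higher still with 1.6. The 30% miss rate therefore applies only if each participant contributes a single correct/incorrect result. That point stands as a limit. It does not rescue the stated calculation, which uses two proportions and no standard deviation, and the Inferential analysis section compares proportions by chi-square.

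Second, the planned meta-analysis across populations would have about 360 per arm. If the effect is common to all three, two-sided power for 75% vs 60% is then about 99%. This softens the harm for the pooled result but leaves the claim for each population wrong, and the populations are to be analysed separately.

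Third, that a one-sided option was chosen is inferred from the numerical match. This is fair. The shortfall does not depend on it, because it follows from the printed inputs alone.

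**Conclusion.** The concern holds. Under the stated inputs, 240 participants per population give 70.1% power, not 80%. The size that matches the stated 80% is 304 complete responses (300 to 330 across standard methods), or about 358 recruited at 15% non-completion. The printed figure agrees exactly with a one-sided 5% test, which the document nowhere plans.

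The conclusion rests on reading the 0.8 labelled beta as power and on taking understanding as one proportion per arm with one response per participant, which is how the calculation is written. It does not show that the trials are too small for an analysis of the mean score. That depends on a standard deviation that the document does not give.

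**What to change.** Rewrite the sample size paragraph in one of two ways.

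**(a) The simplest correction.** State that 120 per arm gives about 70% power for 75% vs 60% at a two-sided 5% level. Replace the beta label with power, and name the two-proportion test in place of the t-test. The cost is a sentence or two and a less favourable stated power. Nothing else in the protocol has to change.

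**(b) Restate the calculation on the 0-7 score.** With a two-sided t-test, 120 per arm gives 80% power for a standardised difference of 0.363. If the standard deviation is 1.6 to 2.0 items, that is 0.363 × 1.6 = 0.58 to 0.363 × 2.0 = 0.73 items, or about 8 to 10 percentage points of the seven-item score. The range for the standard deviation is an assumption, so the protocol would have to state and justify its own value. Inferential analysis would also have to compare mean scores, since it now specifies chi-square tests and risk differences. This is the better match to the outcome as defined, but only if both changes are made.

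Neither route needs more participants. Keeping the 80% claim on the binary assumption would need about 358 recruited per population instead of 282. That is 76 more in each, or 228 across the three, and is far more costly than correcting the wording.

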### Consultation and pilot testing

We will use the same survey template for all populations; however, the “understanding” questions will be appropriately different for each recommendation. We pilot tested the surveys during the pre-trial engagement work to gather feedback from Canadian youth advisors, Cochrane Consumer Network, adult stakeholders, and parent stakeholders. We had 10 youth, 29 adults, and 5 parents pilot test the survey and provide feedback on the time to complete the survey, length of the survey, clarity of questions, Internet difficulties, and any other comments to enhance the survey experience. Revisions were made to the surveys using pilot test feedback until no errors or inconsistencies were detected and the surveys were easily understood. The survey language used for each population is tailored based on the feedback from stakeholders. Pilot test participant results will not be included in the final analysis.

### Statistical analysis

Only participants who submit a complete good quality survey will be included in the analysis. We will exclude all incomplete, speeding (less than 6 min to completion), and straight-lining responses. Each population’s results will be analyzed separately, and we will explore subgroup effects within each group. These subgroups are the topic of recommendation, health literacy level, and English proficiency level of participants. We will also pool the results across populations and conduct a meta-analysis for our primary outcome of “understanding” and other secondary outcomes. In the final analysis, after pooling the results, we will explore for potential interaction related to the recommendation topic and participants’ health literacy level. We will conduct the analyses using IBM SPSS® (Statistical Package for Social Sciences) version 23.

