### Design and setting

There are three online survey links, one for each respective population. Each link contains eligibility questions, the consent form, and study information for youth, parents, or adults. Participants will access the online survey corresponding to their respective population to enter the trials and provide implied consent by participating in the survey. Using the concealed allocation code of the intervention platform, SurveyMonkey (surveymonkey.com), participants will select their geographic region. Participants from each geographic region will be randomized to one of two recommendation topics, and then they will be randomized to a PLR format (intervention) or a SLV format (control) of the recommendation (Fig. 1). The SLV is the original PDF guideline developed and published by an organization, such as the World Health Organization, from where the PLR information was extracted. Participants will complete an online survey consisting of Likert-scale questions, multiple-choice questions, open-ended questions, and demographic information. The survey is anonymous.

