#### Recruitment

Each leading site will run recruitment for the different population groups separately yet with similar and overlapping strategies. We will recruit English-speaking (mother tongue or fluent) participants globally through our experienced RecMap investigator team (https://covid19.recmap.org/about), the Cochrane Consumer Network and various Cochrane networks, guideline co-authors who interact with youth (including the international Young Persons’ Advisory Groups), parents, and adult citizens. We plan to run public recruitment campaigns through identified youth, adult, and parent organizations’ social media platforms (e.g., organizations’ accounts on Twitter, Instagram, and Facebook) and newsletters. Each leading site will be responsible for monitoring its own recruitment, though all investigators will support overall recruitment for the trials (e.g., if recruitment falls behind for one of the populations, other sites will help support recruitment for that group). Surveys will be administered through SurveyMonkey, where participants are screened for eligibility prior to allocation. Previous studies suggest that the target recruitment rates for such trials are achievable in less than 3 months, and we will recruit at least 240 participants per group [18–20].

The average survey completion time is estimated to be 15–25 min, based on stakeholder feedback and pilot testing. As suggested by our stakeholders in the preparation of this trial, we will be inviting participants who complete the survey to enter a draw for a chance to win one of five $50 CAD gift cards for the adult and parents’ populations. The youth group will invite youth participants to enter a draw for one of ten gift cards valued at $25 CAD. This is offered as a gesture and appreciation for completing the survey.

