**Fig. 3 Fig3:**
[figure not shown]
Example of a plain language recommendation summary format for adult participants

Through our pre-trial engagement work, we gathered input from youth (via online workshops) and from adult stakeholders (via online meetings) on high-priority COVID-19 topics and on PLR content and format. Input from youth and adult stakeholders allowed us to choose two recommendations for the trials and refine the PLR format. For the parents’ population, the PLRs were refined from collected feedback during online meetings with parent groups.

All PLRs for the trials were developed from the same template and refined using stakeholder feedback. The youth and parent PLRs’ design and formatting are the same, as these groups gave similar feedback, while the adult PLRs are slightly different.

In the trials, we will ask participants to read one format of a recommendation (PLR or SLV) to which they have been randomly allocated and then answer the online survey that takes an average of 15–25 min to complete.

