#### Secondary outcomes

##### Accessibility and usability

We define accessibility and usability as the ability to find/access and use the presented information. This outcome considers the three following domains: (1) how easy it was to find information, (2) how easy it was to understand the information (perception), and (3) whether the information was presented in a way that could be helpful for making an informed health decision. Participants will be asked to indicate the degree of agreement with six statements, measured using the 7-point Likert scale (1 being strongly disagree, 4 being neutral, and 7 being strongly agree). We will also include 1 open-ended question to get additional input on accessibility and usability. The outcome “overall accessibility/usability of information” will be measured using the average of the 7-point Likert-type scale questions.

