#### Inferential analysis

We will perform a primary analysis including all randomized participants. We will exclude participants who take less than 6 min to complete the survey. For the outcome of understanding, we will use *χ*^2^ tests and risk difference with 95% CIs to compare the proportion of correct responses between groups. For the outcomes of accessibility and satisfaction, we will use *t*-tests and mean differences 95% confidence intervals (95% CIs) to compare means and SDs between the intervention and control groups. Finally, we will present preference as mean (SD) overall and for both trial arms. Skewness, Shapiro-Wilk tests, and histograms will be used to evaluate whether the distribution was shifted toward the same preference in both groups. Levene’s test of equal variances will be used for all *t*-tests and degrees of freedom will be adjusted for *p* < 0.05. We will report all *p*-values to three decimal places, with values less than 0.001 reported as < 0.001. We will consider statistical significance at *p* < 0.05. Furthermore, we will conduct a meta-analysis across the three trials by combining results of the three trials. Our a priori hypothesis is that there is no difference across the three populations despite the differences in population characteristics and slight difference in the presentation formats for each population. However, we will explore differences between trials applying the GRADE approach to evaluating inconsistency which includes the chi-square test, the *I*^2^ value, the overlap in confidence intervals, and the differences in the point estimates of effect for all outcomes [29].

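### The protocol states two incompatible primary analysis sets, and the narrower one rests on post-randomisation exclusions that can depend on the format read

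*Protocol article*

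**What the plan says.** The Statistical analysis section of the protocol article sets the analysis population in two sentences: "Only participants who submit a complete good quality survey will be included in the analysis", then "We will exclude all incomplete, speeding (less than 6 min to completion), and straight-lining responses". Its subsection Inferential analysis opens differently: "We will perform a primary analysis including all randomized participants". The next sentence there is "We will exclude participants who take less than 6 min to complete the survey". That subsection does not mention incomplete or straight-lining surveys.

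The order of events is clear. The survey platform is the place "where participants are screened for eligibility prior to allocation" (Recruitment). Participants then read the format "to which they have been randomly allocated and then answer the online survey that takes an average of 15–25 min to complete" (Intervention and comparison). The two arms read different things: "The SLV is the original PDF guideline developed and published by an organization" (Design and setting), while the intervention is a plain language summary drawn from it.

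The Sample size calculation section asks for 240 participants per population and recruits 282 to allow for 15% non-completion.

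**The concern.** There are two linked problems.

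First, a reader cannot tell which participants the primary test will include. If that is settled after the data are seen, the primary result can depend on the choice.

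Second, the narrower set is defined by what people do after allocation: whether they finish, how long they take, and how they answer. The format is designed to influence ease of use, so finishing may itself be affected by arm. A participant who answers all seven understanding questions and stops before the preference task, which comes after the allocated tasks, is lost from the primary outcome under the complete-survey rule. Randomisation does not protect a comparison of arms filtered in this way. Labelling the groups A and B for the analysts does not restore that protection, and a larger sample or the planned meta-analysis would not average out a bias common to the three trials.

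**Working it through.** **Step 1. The two statements side by side.**

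| Participant | Statistical analysis | Inferential analysis |
|---|---|---|
| Finishes, 6 min or more, no straight-lining | in | in |
| Finishes in under 6 min | out | in by the first sentence, out by the second |
| Finishes, straight-lines | out | in |
| Stops before the end | out | in by the first sentence; the second is silent, since there is no completion time |

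The sets disagree in the last two rows even if the 6-minute sentence is read as qualifying the one before it.

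**Step 2. The plan's own inflation.** 240 / (1 − 0.15) = 282.4, stated as 282, so this figure reproduces. It is the right inflation for a completers-only set. The gap between the two sets is 282 − 240 = 42 people per population (15%), for non-completion alone. The article states no allowance for speeding or straight-lining.

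(Separately, 240 is not what the stated inputs give. For 75% against 60%, two-sided alpha 0.05 and 80% power, a two-proportion calculation gives 152 per arm, 304 in all; 120 per arm matches a one-sided 0.05. That is a different point, but a change of analysis set should be made with it in view.)

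**Step 3. How exclusion could bias the difference.** Let d be the fraction excluded in an arm and g the amount by which retained participants outscore excluded ones there. The mean over all randomised equals the retained mean minus d × g. Hence

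bias of the retained-only difference (PLR − SLV) = d_PLR × g_PLR − d_SLV × g_SLV.

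The document gives only 15% overall, so the splits and gaps below are assumptions.

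- Same gap of 30 points, 15% in each arm: 0.
- Same gap, 10% PLR and 20% SLV: (0.10 − 0.20) × 30 = −3 points; reversed, +3.
- Same gap, 5% PLR and 25% SLV: −6 points; reversed, +6.
- A 15-point gap halves these; no gap gives zero.
- Equal 15% exclusion, but a 30-point gap in PLR and none in SLV: 0.15 × 30 = +4.5 points. Equal counts alone are not reassurance.

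With a true 15-point difference, the 3- and 6-point cases give apparent differences of 12 or 18, and 9 or 21 points.

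On the seven-item scale, a 10%/20% split with a gap of 1 to 2 items gives 0.10 to 0.20 items, or 1.4 to 2.9 points. That is 14–29% of a 10% difference (0.7 items), 10–20% of one correct answer, and about 10–19% of the 15 points (1.05 items) used for sample size.

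**Step 4. Consequence for the test.** Treat the outcome as one binary response per person with 60% correct and 120 per arm. The standard error is √(2 × 0.6 × 0.4 / 120) = 0.063. A 3-point bias raises two-sided type I error from 5% to about 7.6%; a 6-point bias, to about 15.8%.

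**Step 5. Bounds with 15% missing per arm and 75% against 60% among those retained.**

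- Lowest: 0.75 × 0.85 − (0.60 × 0.85 + 0.15) = −2.25 points.
- Highest: (0.75 × 0.85 + 0.15) − 0.60 × 0.85 = +27.75 points.

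**Step 6. Is scoring every missing answer as incorrect a safe remedy?** Take no true difference, a 60% mean in both arms, 10% PLR and 20% SLV missing, and zero credit for the missing.

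- Gap 1 item (0.143): 0.9 × (0.60 + 0.10 × 0.143) − 0.8 × (0.60 + 0.20 × 0.143) = 0.553 − 0.503 = +5 points.
- Gap 2 items (0.286): 0.566 − 0.526 = +4 points.

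This false gain for PLR exceeds the 1.4 to 2.9 points of completers-only bias in the same scenario.

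**The case against.** The strongest reply is that the operative rule can be inferred. The complete-survey sentence opens the parent section, the 6-minute sentence qualifies the all-randomised one, and the inflation to 282 fits a completers-only analysis. On that view one phrase is loose. This explains what was probably meant, but it leaves a primary analysis labelled as including everyone randomised when it would not.

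Three stronger readings are tempting, and the document does not support them.

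- A reader might infer that the exclusions do bias the result. No exclusion data by arm are given, so only the possibility is established. In the scenario where weaker readers leave the standard-language arm, the bias would work against the plain-language format.
- A reader might infer that honest plain-language readers would often finish in under 6 minutes. Under Preference, both arms review the other format before finishing, and both answer the same survey template. Total time therefore covers both formats in each arm, and no completion-time figures by arm can be derived.
- A reader might infer that sincere, uniformly high ratings would be deleted. The usability outcome does invite them ("Participants will be asked to indicate the degree of agreement with six statements"), but the article does not define straight-lining as within one block or across the survey. That definition may sit in an analysis plan not shown.

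Quality filters also have a real purpose in an anonymous survey with self-selected recruits and a gift-card draw, since careless answers attenuate a multiple-choice score. That supports keeping the filter as a sensitivity analysis. The CONSORT commitment goes some way towards counts by arm, and the absence of sensitivity analyses from an article is not held against the plan.

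**Conclusion.** The contradiction is certain and concerns the primary analysis of all three trials. On planning figures it involves about 42 of 282 people per population. That the exclusions follow randomisation is also certain. That they can depend on format follows from the arms reading different documents. Whether they will, how much and in which direction is unknown. The shifts of 1.4 to 6 points and the type I error figures are illustrations on assumed exclusion splits and score gaps; the bounds rest only on the plan's 15% and its 75% and 60%. Bias is zero if exclusion is unrelated to the score, or if it removes equal shares with equal score gaps in both arms.

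**What to change.** State one primary set, in the same words, under Statistical analysis and Inferential analysis: participants analysed as randomised, using all available understanding answers, with no exclusion for completion time, straight-lining or stopping after the understanding items.

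- **Missing understanding answers:** prespecify a primary method, for example multiple imputation under missing at random.
- **Sensitivity analyses:** score missing answers as incorrect, and give best- and worst-case bounds that include people who answered nothing. The bounds are needed because available answers are still a post-randomisation selection, and for someone who leaves early little beyond region, topic and arm may be known. Scoring missing as incorrect should not be the sole primary rule: it can favour the arm with less drop-out, and with 15% missing per arm it lowers power at 141 per arm to 58.2%, against 77.0% if all outcomes were observed.
- **Quality filter:** keep the complete, good-quality set as a prespecified sensitivity analysis, with straight-lining defined before allocation is revealed.
- **Reporting:** give the numbers randomised, not completing and filtered, by arm and reason.

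The cost is an amendment to wording and a few extra runs, with no new data collection. The downside is that some careless responses stay in the primary set and may slightly attenuate the difference.
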